## Statistical methods

### Statistical methods for primary and secondary outcomes {20a}

The central hypothesis that the active treatments reduce the “proportion of cocaine use days” is tested by implementing an analysis of covariance (ANCOVA) with the between-subjects factor treatment groups (i.e. rt-fMRI NFT/placebo, rt-fMRI NFT/ketamine, sham NFT/placebo, and sham NFT/ketamine) once for each treatment (i.e. NFT and ketamine) for the follow-up visit (t3). The initial ANCOVA includes variables that potentially differ between groups at baseline as potential confounding variables, namely age, gender, substance use, and severity of dependence. To retain the simplest model, all the baseline variables that do not contribute to the outcome variable ‘proportion of cocaine use days’ are excluded from the model. Should none of the baseline variables that differ between groups contribute to the outcome variable, an analysis of variance (ANOVA) is performed. Post-hoc tests are adequately corrected for multiple comparisons.

Changes in glutamate levels in the NAcc due to the ketamine infusion on intervention visit I (t1) are analysed by applying an ANOVA for repeated measurements as not many dropouts for one of the pre-ketamine and post-ketamine glutamate assessments are expected. The main source of dropouts is expected to be of technical nature, causing insufficient data quality of the ^1^H-MRS, while dropout due to lack of compliance between the two measurements is less plausible since they take place on the same day. The ANOVA for repeated measurements includes the between-group factor treatment group (i.e. rt-fMRI NFT/placebo, rt-fMRI NFT/ketamine, sham NFT/placebo, and sham NFT/ketamine) and the within-group factor time (pre-ketamine infusion vs. post-ketamine infusion). Post-hoc test is adequately corrected for multiple comparisons. To test for sustained effects of the ketamine infusion on glutamate concentrations in the NAcc between intervention visit I (t1) and intervention visit II (t2), a multilevel analysis is applied that allows to (i) analyse multiple events in one model, (ii) include subjects with incomplete data sets, (iii) account for different time intervals between the events (7 to 14 days).

The transfer effect of the reward imagery rt-fMRI NFT from the first to the second session is analysed by comparing the percent signal change in the practice run from the first reward imagery rt-fMRI NFT session (t1) and the transfer run from the third reward imagery rt-fMRI NFT session (t2) in an ANOVA for repeated measurements with a between-subject factor treatment group (i.e. rt-fMRI NFT/placebo, rt-fMRI NFT/ketamine, sham NFT/placebo, and sham NFT/ketamine) and the within-group factor time (first session at t1 vs. third session at t2). Post-hoc tests are adequately corrected for multiple comparisons. To test the impact of fatigue or of earlier reward imagery rt-fMRI NFT success on the transfer effect, an exploratory analysis with a multilevel analysis is performed that enables to include multiple events, in this case the transfer run from the first reward imagery rt-fMRI NFT session and the practice run from the third reward imagery rt-fMRI session, thereby accounting for different time intervals between those four events.

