**Discussion:**

We expect both interventions to have a positive effect on the proportion of cocaine use days. We predict glutamate levels in the reward system to increase with the ketamine infusion and to reduce craving, a re-enhanced sensitivity towards natural rewards resulting from the rt-fMRI NFT, and synergistic effects of the combined interventions. This neurobiologically informed approach has the potential to open new avenues for the treatment of CUD through individualised and integrated pharmaco-psychotherapy.

Trial registration.

NCT06125054 ClinicalTrials.gov. Registered on October 26, 2023.

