### Trial design {8}

The trial adopts a randomised, placebo-controlled, double-blind, parallel-group, single-centre design with a superiority framework. The treatment combination among the four arms, each consisting of 30 participants, is depicted in Fig. 1.

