## Interventions

### Explanation for the choice of comparators {6b}

Two forms of interventions are combined and compared: a single dose of ketamine and a reward imagery rt-fMRI NFT. Both interventions are placebo-controlled, which leads to four study arms with the following intervention combinations: (i) rt-fMRI NFT/placebo, (ii) rt-fMRI NFT/ketamine, (iii) sham NFT/placebo, and (iv) sham NFT/ketamine. This study group allocation allows for comparing each active treatment to its placebo treatment and, in addition, the combination of both interventions to a placebo study arm, that is, study arm (iii) sham NFT/placebo.

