### Sample size {14}

Sample size was determined by power analysis (G*Power 3.1) and primarily focused on ^1^H-MRS, the most critical procedure in this project to estimate the required number of participants to detect between- and within-subject effects as well as interaction of those. Prior ^1^H-MRS studies that reported significant glutamate differences with effect sizes measured in psychiatric populations within the striatum showed effect sizes of *d* = 1.6 [76], *d* = 0.89 [12], *d* = 1.93 [77], or measured in other brain regions in tobacco use disorder *d* = 1.03 [78]. Thus, assuming a conservative effect size of *d* = 0.80, an α-error probability of 5%, and a conservative power estimation of 80%, a total sample size of 21 individuals with CUD per group (total sample of 84) would be required to detect a significant group effect between experimental and control groups. Again, assuming an effect size of *d* = 0.80 (*f* = 0.40, respectively) for within-subject comparisons before and after intervention, an α-error probability of 5%, and a conservative power estimation of 80%, indicates that a total number of 111 subjects would be necessary to detect a significant within-factor effect in an ANCOVA model. To account for potential dropout, we will recruit in total 120 participants.

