## Assignment of interventions: allocation

### Sequence generation {16a}

Each participant gets a subject code, which is generated by the investigator at study inclusion and is individually allocated. The randomisation of the four study arms is counter-balanced with a 1:1:1:1 allocation ratio as per a computer-generated randomisation schedule using the method of minimisation, with age, gender, and severity of CUD based on the assessment of the DSM-5 criteria by the structural interview MINI [75] at the screening visit (t0) (mild and moderate vs. severe) as binary minimisation variables.

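### The four arms form a 2x2 layout, but the primary model does not say which treatment contrasts it tests, and no planned contrast can test the predicted synergy

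*Protocol article*

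**What the plan says.** **Design.** The section on the choice of comparators lists the arms as "i) rt-fMRI NFT/placebo, (ii) rt-fMRI NFT/ketamine, (iii) sham NFT/placebo, and (iv) sham NFT/ketamine". Trial design describes them as "each consisting of 30 participants", and Sequence generation calls the randomisation "counter-balanced with a 1:1:1:1 allocation ratio". The article labels the design parallel-group and does not use the word factorial.

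**Primary model.** Under Statistical methods {20a}, the ANCOVA for the proportion of cocaine use days has a between-subjects treatment factor whose listed levels are all four arms. The same sentence says the analysis is done "once for each treatment (i.e. NFT and ketamine) for the follow-up visit (t3"). Post-hoc tests are to be corrected for multiplicity; neither the set of contrasts nor the method is given.

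**Mechanistic models.** For glutamate at t1, "The ANOVA for repeated measurements includes the between-group factor treatment group", again with the four arms as levels, crossed with time. The NFT transfer analysis has the same structure. Neither carries the per-treatment qualifier.

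**Combination.** The abstract predicts "synergistic effects of the combined interventions", and the main Discussion aims for the combination to boost the stand-alone effects. The comparators section says the allocation permits comparing "the combination of both interventions to a placebo study arm", namely sham NFT/placebo. No ketamine x NFT term or contrast appears anywhere. The interaction mentioned under Sample size is between-subject by within-subject, which is a different thing.

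**The concern.** Two things are wrong with the text as it stands.

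First, the primary sentence cannot be carried out as written. If the factor has four levels, running the model once for NFT and once for ketamine gives the same model twice. If the model is meant to be run per treatment, the factor should have two levels and the list of four arms is wrong. Analysts could therefore choose between a 3-df test, a set of pairwise tests and two marginal tests, and these can lead to different conclusions from the same data.

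Second, a declared expectation of the trial has no test. Synergy means that the combination does more than the sum of the two separate effects. Only the ketamine x NFT contrast measures that. Combination against double placebo measures the two effects and any interaction added together, so it can be strongly significant when the interaction is zero.

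**Working it through.** **Inputs.** From the article: four arms, 30 per arm, N = 120, 1:1:1:1, and "an α-error probability of 5%, and a conservative power estimation of 80" per cent. It gives no effect size for cocaine use days. Its only planning value, d = 0.80, is for glutamate by 1H-MRS. I therefore take d = 0.5 to 0.8 as an assumed range. Further assumptions: two-sided 5%, complete data, no precision gain from covariates, error df = 120 - 4 = 116.

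**The plan's own figure.** The 21 per group under Sample size is reproduced by a one-sided two-sample t-test at d = 0.80 (power 0.817). Two-sided, 26 per group would be needed. It concerns glutamate, so there is no stated power for the primary cocaine outcome to reproduce.

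**What the combination contrast measures.** Write *k* for the ketamine effect under sham NFT, *f* for the NFT effect under placebo, and *I* for the interaction, i.e. the difference of differences.
- Combination minus double placebo = *k + f + I*
- Interaction = combination - (sham NFT/ketamine) - (NFT/placebo) + double placebo = *I*

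Let *k* = *f* = 0.5 SD and *I* = 0. The first contrast is then 1.0 SD. Its noncentrality is n x d²/2 = 30 x 1.0/2 = 15 on 1 and 116 df. Power is 97% at 5%, and 88% at 0.05/6, with no synergy present.

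**Power for one active treatment under each reading** (noncentral F):
- Marginal main effect, 60 v 60: noncentrality N x d²/4, 1 df. At d = 0.5 this is 120 x 0.25/4 = 7.5; at d = 0.8 it is 120 x 0.64/4 = 19.2.
- Four-level omnibus: the same noncentrality, 3 df.
- One pairwise comparison, 30 v 30: noncentrality n x d²/2. At d = 0.5 this is 30 x 0.25/2 = 3.75; at d = 0.8 it is 30 x 0.64/2 = 9.6.

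| Test | d = 0.5 | d = 0.8 |
|---|---|---|
| Main effect, 60 v 60, 5% | 77.5% | 99.1% |
| Main effect at 2.5% (first Holm step) | 68.0% | 98.2% |
| Omnibus F, 3 df | 60.7% | 96.4% |
| Pairwise, unadjusted | 48.4% | 86.7% |
| Pairwise, 0.05/3 | 31.5% | 74.7% |
| Pairwise, 0.05/6 | 23.2% | 66.0% |

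**Power of the interaction.** For a difference of differences D, noncentrality is n x D²/4.
- D = 0.5 SD: 30 x 0.25/4 = 1.875, power 27%.
- D = 0.8 SD: 30 x 0.64/4 = 4.8, power 58%.
- About 1.03 SD is needed for 80%.

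The standard error of the interaction is sqrt(4/30) = 0.365 SD, twice that of a main effect, sqrt(4/120) = 0.183 SD.

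**The case against.** The per-treatment wording has a sensible reading: two ANCOVAs, each comparing an active treatment with its placebo over about 60 v 60 participants. The comparators section supports this, since it says the allocation lets each active treatment be compared with its own placebo. A four-level factor also fits the same cell means as a 2x2 model with interaction, so both main effects and the interaction can be extracted as contrasts. The article prescribes neither an omnibus decision rule nor 30 v 30 tests, and an analysis plan that is not shown may name the contrasts.

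Most of this stands. A reader might infer that the main effects are bound to be tested inefficiently. The document does not support that; the loss depends on which reading is applied, and at d = 0.8 the omnibus test costs only about 3 percentage points. A reader might also count the tests under the primary outcomes heading and quote a familywise error rate. The article does not fix how many cocaine-use tests there are, names one primary efficacy value, and describes the glutamate and transfer outcomes as mechanism of action, so no such figure is offered here.

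It can also be said that the objectives ask only whether the combination beats placebo, which combination v double placebo does answer, and that nothing in the article says this contrast will be reported as synergy. That is correct. It does not remove the gap: synergy is predicted, and no named analysis addresses it.

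The objection does not make the primary sentence consistent. An unseen plan cannot be assumed to correct a model that the article itself states.

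**Conclusion.** The concern holds in this form. The primary contrasts are unclear because the four-level factor and the per-treatment wording conflict, the glutamate and transfer models repeat the four-level factor, and the predicted synergy has no test. These points rest on the text alone.

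The size of any power loss is conditional. For one active treatment it runs from almost nothing, if two marginal ANCOVAs are meant, to a drop from 78% to 61% (omnibus) or 23-48% (pairwise, from Bonferroni over six to unadjusted) at an assumed d = 0.5. At d = 0.8 the drop is from 99% to 96% or 66-87%. The 97% chance of a significant combination contrast without synergy rests on two additive effects of 0.5 SD, also an assumption. That the contrast mixes the three components is algebra and does not depend on it.

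**What to change.** State one ANCOVA for cocaine use days at t3 with effect-coded ketamine, effect-coded NFT, ketamine x NFT and the covariates. Effect coding, or explicit marginal contrasts, matters: with 0/1 coding and an interaction in the model, the treatment coefficients are 30 v 30 simple effects.

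- **Confirmatory:** the two marginal (60 v 60) main effects, with Holm control at 5%.
- **Synergy:** the interaction estimate with its confidence interval, named as the only evidence on synergy.
- **Shown beside it:** the simple effects and combination v double placebo.
- **Mechanistic models:** the same coding crossed with time, with ketamine x time as the contrast of interest for glutamate and NFT x time for transfer.

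The cost is wording, settled before unblinding; no data collection changes. Three downsides should be stated. Main effects average over the other factor, which is why simple effects must accompany them. Holm costs some power: 68% instead of 78% at d = 0.5 when only one treatment works, still above the omnibus test. Interaction power is low at N = 120 (27% for a 0.5 SD and 58% for a 0.8 SD difference of differences), so a non-significant interaction must not be read as evidence against synergy.

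### Acute glutamate and neurofeedback transfer are tested by a four-group comparison of unadjusted change scores; adjusting for the baselines already collected, with named contrasts, would be more precise at almost no cost

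*Protocol article*

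**What the plan says.** Protocol article, Statistical methods for primary and secondary outcomes {20a}:

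- **Glutamate at t1.** "The ANOVA for repeated measurements includes the between-group factor treatment group", with the four arms as levels, and a time factor of two levels (before and after infusion). The stated aim is change caused by the infusion.
- **NFT transfer.** The session-1 practice run and the session-3 transfer run are compared "in an ANOVA for repeated measurements with a between-subject factor treatment group", again with four arms and two times.
- **Follow-up.** Both rely on post-hoc tests corrected for multiplicity. Neither the contrasts nor the correction is named.

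The cocaine-use ANCOVA in the same section is run separately for ketamine and for NFT; the two mechanistic outcomes have no such provision. Explanation for the choice of comparators {6b} says the design supports each active treatment against its own placebo, and the combination against sham/placebo. Sample size {14} states that "a total number of 111 subjects would be necessary to detect a significant within-factor effect in an ANCOVA model".

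**The concern.** With two time points, the group-by-time F test is identical to a one-way comparison of change scores across four arms, on 3 df. Two features stand out.

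1. **The baseline is subtracted, not adjusted for.** Both outcomes have a true pre-treatment value. The first spectroscopy scan precedes the first NFT session and the infusion, and the session-1 practice run precedes any feedback.
2. **The test asks whether any of four arms differ.** The stated question for glutamate is ketamine against placebo, which is 60 against 60. For transfer, the natural contrast is real against sham NFT, also 60 against 60.

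Both outcomes are listed under Primary outcomes, and the trial was sized on spectroscopy. Section 20a also expects some spectra to be lost to poor quality, so precision matters.

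**Working it through.** **Inputs from the protocol.** Four arms of 30, 1:1:1:1, N = 120; planning effect "assuming a conservative effect size of *d* = 0.80" (f = 0.40); alpha 5%; power 80%.

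**Assumptions.** The pre-post correlation r is not given; I use 0.3, 0.5 and 0.7. Pre and post variances are taken as equal. I read d as the ketamine-placebo difference in SDs of one measurement. d = 0.5 is my own smaller-effect case.

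**The protocol's figure first.** With noncentrality λ = N × f² = 0.16N, 80% power needs N = 73 for a 3-df test and N = 52 for a 1-df test. The stated 111 appears only with 10 numerator df, which a four-arm, two-time design does not have. So the 111 cannot be tied to the planned repeated-measures ANOVA or to a four-arm ANCOVA. That is a separate matter and does not make 120 too small for this test.

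**Residual variance, in units of one measurement's variance.**

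- Change score: v = 2(1 − r)
- Baseline-adjusted: v = 1 − r²
- Ratio, adjusted to change: (1 + r)/2 = 0.65, 0.75, 0.85

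The ratio needs equal variances; the ordering does not. With SDs s1 (pre) and s2 (post), change variance minus adjusted variance is (s1 − r·s2)², which is never negative. The covariate costs one residual df, which I ignore by using N − 4 throughout.

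**Additive ketamine effect.** λ = N·d²/(4v). For example, d = 0.5, r = 0.5, N = 120: λ = 7.5/1 = 7.5 for change and 7.5/0.75 = 10 adjusted.

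| d | r | 3-df change (planned) | 1-df change | 3-df adjusted | 1-df adjusted |
|---|---|---|---|---|---|
| 0.8 | 0.3 | 87.8% | 95.7% | 97.7% | 99.5% |
| 0.8 | 0.5 | 96.4% | 99.1% | 99.3% | 99.9% |
| 0.8 | 0.7 | 99.9% | 100% | 100% | 100% |
| 0.5 | 0.3 | 45.5% | 63.1% | 65.2% | 81.2% |
| 0.5 | 0.5 | 60.7% | 77.5% | 74.5% | 88.0% |
| 0.5 | 0.7 | 84.3% | 93.9% | 90.1% | 96.7% |

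At d = 0.5 and r = 0.5 the gain splits into 16.8 points from 3 df to 1 df (60.7% to 77.5%) and 10.5 points from adjustment (77.5% to 88.0%).

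With an assumed 10% of spectra unusable (N = 108), the planned test at d = 0.8 still has 83.6%, 94.3% and 99.7%. At N = 120 it drops below 80% only when r is near zero (72.6% at r = 0).

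**Effect in the combination arm only** (0.8 SD, r = 0.5, N = 120). Arm means are 0, 0, 0 and d.

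- 3-df change test: λ = 120 × 0.64 × (3/16)/1 = 14.4, power 89.4%
- 3-df adjusted test: λ = 14.4/0.75 = 19.2, power 96.4%
- 1-df adjusted ketamine contrast: the marginal effect is halved to 0.4, λ = 120 × 0.16/(4 × 0.75) = 6.4, power 70.8%
- Adjusted combination versus sham/placebo contrast: λ = 30 × 0.64/(2 × 0.75) = 12.8, power 94.4% at an unadjusted 5%

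Adjustment helps in both scenarios. Moving to a single marginal contrast helps in the first and hurts in the second.

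**The case against.** **The planned test is valid and adequately powered on the protocol's terms.** Repeated-measures ANOVA on two time points is sound in a randomised trial. At d = 0.80 it stays above 80% power across r = 0.3 to 0.7. This stands. A reader might infer that the analysis leaves the trial underpowered, but that needs an effect smaller than the protocol assumes. It can be added that the planning value rests on earlier studies chosen because they reported significant differences, which tends to inflate effects. That is a reason to look at smaller values, not proof that they apply.

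**Synergy is predicted.** The Abstract and Discussion expect it, and the combination is a stated comparison. An NFT session falls between the two spectroscopy scans, and the infusion falls between NFT sessions 1 and 3, so either outcome could depend on both factors. This also stands. A reader might infer that a 1-df ketamine or NFT test should simply replace the four-group test; the combination-only figures show that this can lose power.

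**The post-hoc tests may include the right contrast, and an analysis plan may name it.** Possible, and silence on the exact contrasts is not the point here. What section 20a does fix is the four-group change-score model, and it leaves the main mechanistic question to a follow-up test that carries a multiplicity correction.

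**NFT transfer has no inputs.** True. No effect size or run-to-run correlation is given, so the argument there is structural only.

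**Conclusion.** The point holds as an improvement in efficiency and clarity, not as the correction of an error. Section 20a commits both mechanistic outcomes to a 3-df test on unadjusted change scores, while the stated glutamate question is the ketamine effect and section 14 names a different model.

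Baseline adjustment alone would need 65%, 75% or 85% of the sample size at r = 0.3, 0.5 or 0.7, whichever way the effect is spread over the arms. At the protocol's d = 0.80 the total gain with a 1-df contrast is small at r = 0.5 (3.5 points) and 11.7 points at r = 0.3. It is large, at 27.3 points for r = 0.5, only if the effect is about 0.5 SD and additive. All of this rests on assumed correlations and equal variances, and it covers glutamate only. The marginal contrast is a trade-off and should be presented as one.

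**What to change.** Amend section 20a as follows.

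- **Glutamate at t1:** ANCOVA of the during-infusion value (which 20a labels post-infusion) on the pre-infusion value, with ketamine, NFT, their interaction and the allocation factors (age, gender, severity). Name the ketamine contrast in advance.
- **NFT transfer:** ANCOVA of the session-3 transfer run on the session-1 practice run, with the same terms. Name the NFT contrast in advance.
- **Both:** keep the interaction and the combination versus sham/placebo contrast as prespecified tests. State their order or multiplicity correction, and say openly that the marginal contrast loses power if the effect is confined to the combination arm.
- **Section 14:** make the named model agree with 20a.

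No further measurements or participants are needed. At submission recruitment was under way and three participants had completed, so the change must be made before unblinding. If it counts as a substantial modification, section {25} requires ethics approval.

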### Interim analyses {21b}

No interim analyses are planned because (a) it is not a safety measurement and (b) no statement to clinical efficacy can be made.

